### Outcome measurements

2.10

The following outcomes will be assessed by trained assessors at specific visit timepoint, as shown in Table 2.

#### Primary outcomes

2.10.1

1.The changes in cognitive function will be assessed by Alzheimer Disease Assessment Scale-cognitive subscale (ADAS-cog).^[35]^ The total score of ADAS-cog ranges from 0 to 70, and a higher score indicates more severe dysfunction.2.The neurological status will be evaluated by National Institute of Health stroke scale (NIHSS).^[36]^ The maximum score of NIHSS is 42, and a higher score represents more severe neurological deficit.

#### Secondary outcomes

2.10.2

1.The Mini-Mental State Examination (MMSE) scale^[37]^ for assessing the extent of dementia.2.The Activities of Daily Living (ADL)^[38]^ score for rating quality of life.3.The changes in Traditional Chinese Medicine (TCM) symptoms will be assessed based on TCM syndrome scale score. The efficacy will be measured by a reduction (reduction = (before treatment score – after treatment score)/before treatment score × 100%) in the following scale: clinical cure: reduction ≧95%, markedly effective reduction ≧70%, effective: reduction ≧30%, invalid: reduction <30%.^[39]^4.Serum concentration of hypersensitive C-reactive protein (Hs-CRP), homocysteine (HCY) and neuron-specific enolase (NSE). The morning fasting venous blood will be obtained from participants. Separated serum will be stored at −80°C for further test.

### Safety measurements and assessments

2.11

Safety measurements (as described in Table 2) side effects and adverse events will be monitored and recorded, including event, date of onset, severity, duration, and relationship to the study drug. Serious adverse events will be reported to the ethics committee of Xiyuan hospital within 24 hours and followed until they are adequately resolved.

### Data management and quality control

2.12

To protect the anonymity and privacy of participants, participants’ name or identifying information will remain anonymous. An independent organization will be responsible for the data management. Data will be imported into the database by 2 independent staffs. After confirming blindness, the database will be locked. Before this trial began, all the staffs will receive a standard training that covered the clinical trial process, the administration of the assessments, the case report form completion, and the use of study granules. Xiyuan Hospital, the supervisor, will audit the trial conduct of each clinical trial center at least once a month.

### Statistical analysis

2.13

All the data will be analyzed by a statistician using SPSS 19.0 software (IBM Corp., Armonk, NY) in a blinded manner. Outcomes will be analyzed in accordance with the intention-to-treat (ITT) principle. Missing values will be handled by the multiple imputation method.^[40]^ Homogeneity of Baseline characteristics will be analyzed with *t* test for continuous variables and χ^2^ test for categorical variables, or with Wilcoxon Mann–Whitney test. Primary outcomes, and secondary outcomes will be analyzed by covariance with treatment groups as factors and baseline values as covariates. Mean difference will be used to illustrate the effect size.

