**Methods::**

This is a multicenter, randomized, blind, controlled trial. A total of 196 eligible patients will be assigned to receive Ginkgo biloba extracts (GBEs) plus SMYZD granule or GBEs plus SMYZD mimetic granule in a 1:1 ratio. The duration of the trial will be 12 weeks, and a follow-up will be performed at the 24th week. The primary outcomes are the National Institute of Health stroke scale (NIHSS) and the Alzheimer Disease Assessment Scale-cognitive subscale (ADAS-cog). The secondary outcomes include the Mini-Mental State Examination (MMSE), the traditional Chinese Medicine (TCM) syndrome scale, Activities of Daily Living (ADL), concentrations of hypersensitive C-reactive protein (Hs-CRP), neuron-specific enolase (NSE) and homocysteine (HCY) in serum. Researchers will record any adverse events throughout the trial.

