### Recruitment

2.4

Participants will be recruited from Xiyuan hospital and community healthcare centers of Jingzhuang Town and Shen Jiaying Town, Yanqing District, Beijing. The enrollment will be advertised through hospital posters and oral promoting by researchers. The recruitment is now on-going. Eligible participants will sign the informed consent form and receive a copy one which contains the contact telephone of the investigator. A dedicated phone line will response inquiries about joining in the project (8 am to 6 pm, from Monday to Friday).

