### Sample size calculation

2.5

The sample size was calculated based on the mean change from baseline in the Alzheimer Disease Assessment Scale-cognitive subscale (ADAS-cog) score. The previous study show that 1.5-point could detect a difference on ADAS-cog,^[33]^ thus we set δ = 1.5. With α at 0.05, β = 0.2 (80% power), s = 3.5, and δ = 1.5. As a result, 85 participants were needed in each group. Considering a discontinuation of 15%, the sample size required for the study was 98 per group.

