### Randomization and blinding

2.6

Randomization will be stratified by study center, with allocation ratio of 1:1 for each group. A random list of numbers will be generated using SAS software (version 9.2) by an independent statistician at the Good Clinical Practice (GCP) institute of the Xiyuan Hospital, who is not involved in the data collection or analysis. Research drugs will be numerically labeled and packaged according to the random numbers by the statistician of GCP institute. Participants will be allocated randomly into SMYZD group or control group according to the visit sequence. Participants, caregivers, investigators, data collectors and outcome assessors in this trial will remain blinded to allocated intervention until the study completion. Unblinding is permissible under the following circumstance:

(1)Participants develop another severe disease that need to be treated urgently;(2)Serious adverse event (SAE).

Withdrawal occurs when a participant's allocation or intervention is revealed.

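### Randomisation is stratified by study centre, but the stated ANCOVA leaves centre out and may lose precision

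*Protocol article*

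**What the plan says.** Section 2.6 (Randomization and blinding) states: "Randomization will be stratified by study center, with allocation ratio of 1:1 for each group". Centre is the only stratification factor named. Section 2.4 (Recruitment) describes sites of two kinds: "Participants will be recruited from Xiyuan hospital and community healthcare centers of Jingzhuang Town and Shen Jiaying Town". This suggests three centres, but the article does not give the number.

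Section 2.13 (Statistical analysis) gives one model for all outcomes. The primary and the secondary outcomes alike "will be analyzed by covariance with treatment groups as factors and baseline values as covariates". The effect measure is the mean difference. Nothing elsewhere in the article adds a centre term, a stratified test or a sensitivity analysis by centre.

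Section 2.5 (Sample size calculation) is based on change from baseline in ADAS-cog: "With α at 0.05, β = 0.2 (80% power), s = 3.5, and δ = 1.5".

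**The concern.** When arms are balanced within centre, differences between centres largely cancel out of the treatment comparison. A model without centre does not credit that: it leaves between-centre variation in the residual and counts it as error. The standard error is then larger than the true sampling variability, the confidence interval is too wide and the test is conservative. If the lists do not force balance within centre, chance imbalance adds real noise to the comparison, and a centre term would remove it. On both routes, leaving centre out costs precision whenever centre predicts outcome beyond the baseline score.

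This is plausible here. The sites are a hospital and town community health centres, and the ADAS-cog and NIHSS are scored by raters, so case mix, course of disease and scoring may differ by site. The planned power also has little slack, as the working shows.

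**Working it through.** **Inputs from the article.** Difference 1.5 and SD 3.5 on ADAS-cog, alpha 0.05, power 80%, 85 per group before dropout, 15% discontinuation, 98 per group (section 2.5). Alpha is taken as two-sided, because that reproduces the stated size.

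**Input that is an assumption.** f, the share of residual variance after baseline adjustment that centre explains. The documents give no figure. Range used: 0 to 0.15.

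**1. The plan's own figure.** n per group = 2 × [3.5 × (1.960 + 0.842) / 1.5]² = 85.47, which rounds up to 86. The article states: "As a result, 85 participants were needed in each group". That agrees to within one patient. A one-sided test would need 68 and does not match.

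**2. Evaluable patients.** The article states: "Considering a discontinuation of 15%, the sample size required for the study was 98 per group". This matches 85 × 1.15 = 97.75; dividing instead, 85 / 0.85 = 100. If 15% of 98 discontinue, 98 × 0.85 = 83.3, so about 83 per arm remain.

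**3. Effect of omitting centre, with arms balanced within centre.**

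- SE reported without centre: 3.5 × √(2/83) = 0.5433.
- True SE, equal to the SE with centre in the model: 0.5433 × √(1 − f).
- Overstatement of the SE: 1/√(1 − f) − 1.
- True type I error without centre: 2 × [1 − Φ(1.96/√(1 − f))].
- Power without centre: Φ[(1.5 − 1.96 × 0.5433) / true SE] = Φ(0.4351 / true SE).
- Power with centre: Φ(1.5 / true SE − 1.96).

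| f (assumed) | True SE | SE too large by | Type I error without centre | Power without centre | Power with centre |
|---|---|---|---|---|---|
| 0 | 0.5433 | 0% | 5.0% | 78.8% | 78.8% |
| 0.05 | 0.5295 | 2.6% | 4.4% | 79.4% | 80.9% |
| 0.10 | 0.5154 | 5.4% | 3.9% | 80.1% | 82.9% |
| 0.15 | 0.5009 | 8.5% | 3.4% | 80.7% | 85.0% |

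Total SD is held at 3.5, so the true SE shrinks as f grows. This is why power rises slightly even without centre. The comparison that matters is across each row.

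**4. Simulation check.** ANCOVA with and without centre was simulated for 170 patients in three centres of 84, 44 and 42 (assumed sizes), with 6000 runs per scenario.

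- *Blocks of 4 within centre, f = 0.10:* type I error 0.038 without centre and 0.048 with it; power 80.2% against 83.0%.
- *Simple lists within centre:* type I error without centre was 0.051, 0.052 and 0.048 at f = 0.05, 0.10 and 0.20, so it stays near 5%. Power at f = 0.10 was 78.2% without centre against 81.9% with it. At f = 0 both models gave 0.058; both are correctly specified there, so this is simulation noise.

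**The case against.** Several points count against a stronger claim.

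- **Balance within centre is not stated.** A reader might infer that the standard errors and p-values are certain to be too large. That requires restricted lists, such as blocks, within each centre. Section 2.6 mentions 1:1 allocation, a computer-generated list and assignment in order of visits, but no blocks. This stands: the SE and type I columns are conditional. The loss of precision is not, as the simple-list simulation shows.
- **The centre share may be small.** The model already adjusts for each patient's baseline score, which absorbs much of any stable difference between sites. Assessors are trained (section 2.10), and staff training is standard with each centre audited at least monthly (section 2.12). This also stands, and it is why the range must start at zero, where nothing is lost.
- **Power is not clearly short.** The planned SD is for change from baseline. ANCOVA on baseline is generally at least as efficient as analysing change, so the residual SD may be below 3.5. The documents do not allow this to be quantified. Even in the table, power without centre is close to the planned 80%.
- **The article is a summary.** The full protocol or analysis plan may include centre, so one cannot infer that the trial will certainly be analysed without it. But section 2.13 goes beyond naming a method: it lists the factor and the covariate. If a fuller document adds centre, this sentence misdescribes it. By contrast, the article describes no imputation model, so there is no misstatement to correct on that point.

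It would also be wrong to infer that the result is biased or the false-positive rate inflated. Neither follows from omitting a stratification factor in this model.

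**Conclusion.** The point holds in a limited form. The stated ANCOVA omits the only factor by which patients are randomised, and it may lose precision as a result. For an assumed centre share of 0% to 15%, the loss runs from nothing to about 4 percentage points of power. The overstatement of the SE runs from 0% to 8.5%, provided arms are balanced within centre. These figures rest on SD 3.5, a difference of 1.5, 83 evaluable per arm and a normal approximation. The error is in the conservative direction, so validity is not in question. It merits correction because the remedy is nearly free.

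**What to change.** In section 2.13, state the model for the primary outcomes and the continuous secondary outcomes as: 'ANCOVA with treatment group and study centre as fixed factors and the baseline value as covariate'. Fix this before unblinding, so that the choice of covariates cannot be questioned later.

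The cost is one sentence and one degree of freedom per centre beyond the first: two if there are three centres, as section 2.4 suggests. Sample size and trial conduct do not change.

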## Discussion

3

Vascular dementia is an enormous, worldwide public health problem. Traditional Chinese medicine is an important complementary and alternative medicine, which has been used for treatment of dementia-like symptoms for centuries. SMYZD, a Chinese herbal formula, was used as an adjuvant treatment of VaD in clinical practice in China. Preclinical studies support that SMYZD could intervene in complicated molecular pathways underlying the pathogenesis of VaD. The main aim of this study is to investigate the effect of SMYZD as an adjuvant role in the treatment of AD.

In the present study, besides using the ADAS-cog, MMSE, ADL and TCM symptom scales to assess the clinical curative effect on cognitive function, NIHSS will be introduced to evaluate neurological status. In addition, we monitor the serum concentration of Hs-CRP, NSE and HCY to explore the possible mechanism of SMYZD combined with GBEs on treating VaD.

This study also has some limitations. For example, this study is limited to 1 region (Beijing). It is unclear whether our findings will be representative of other regions of China.

In conclusion, findings of this study are expected to provide evidence for efficacy and safety of SMYZD as an adjuvant treatment of VaD.

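### ANCOVA with a mean difference and no stated transformation also covers serum Hs-CRP, NSE and HCY; if these are clearly right-skewed, it loses precision that a log-scale analysis would keep (minor)

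*Protocol article*

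**What the plan says.** Section 2.13 of the protocol article (Statistical analysis) gives one rule for every efficacy outcome: "Primary outcomes, and secondary outcomes will be analyzed by covariance with treatment groups as factors and baseline values as covariates". The effect measure follows: "Mean difference will be used to illustrate the effect size". Section 2.10.2 lists serum Hs-CRP, HCY and NSE as the fourth secondary outcome, so the rule covers them.

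No transformation, ratio measure or rank-based alternative is named for any outcome. Section 2.13 does name a rank test, in the words "or with Wilcoxon Mann–Whitney test", but only for comparing the groups at baseline.

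The Discussion gives the purpose of these measurements: "we monitor the serum concentration of Hs-CRP, NSE and HCY to explore the possible mechanism of SMYZD combined with GBEs on treating VaD". Section 2.5 sizes the trial on ADAS-cog alone. No SD, target effect or power is given for any serum marker.

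**The concern.** Serum concentrations are positive and may have a long right tail. When they do, a few high values supply much of the variance of an untransformed analysis, the interval around the mean difference widens, and a real proportional change is harder to detect. ANCOVA on log values is the usual remedy.

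At stake is the precision of the only mechanistic data among the listed outcomes. A scale chosen after the results are known would also be open to the charge that it was chosen for the result. The efficacy conclusions on ADAS-cog and NIHSS are not involved.

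**Working it through.** **The plan's own figure.** Section 2.5 states "With α at 0.05, β = 0.2 (80% power), s = 3.5, and δ = 1.5". The standard formula gives n = 2 × (1.960 + 0.842)² × 3.5² / 1.5² = 85.5 per arm, against 85 stated. Then 85 × 1.15 = 97.75, which is the stated 98. The figure reproduces, but it concerns ADAS-cog only and says nothing about the markers.

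**Inputs for the markers**
- From the document: 98 per arm and 15% discontinuation, so 98 × 0.85 = 83.3, taken as 83 per arm with data; α = 0.05, used two-sided because that fits the stated sample size.
- Assumed, because the document gives nothing: log-normal baseline and follow-up, log-scale SD σ from 0.3 to 1.2, log-scale baseline correlation ρ = 0.5 (0.3 to 0.7 in the second check), and a 30% reduction, that is a ratio of 0.70.

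**Check 1: fixed 30% reduction, 83 per arm, ρ = 0.5.** There were 3,000 simulated trials per setting, each analysed by ANCOVA on raw and on log values.

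| σ | Raw-scale power | Log-scale power |
|---|---|---|
| 0.5 | 99.7% | 99.9% |
| 0.8 | 77% | 91% |
| 1.0 | 51% | 75% |
| 1.2 | 33% | 60% |

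Repeat runs agreed within 2 percentage points.

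The log-scale column can be confirmed by hand. SE = σ × √(1 − ρ²) × √(2/83), and power ≈ Φ(|ln 0.70| / SE − 1.960), with |ln 0.70| = 0.357:
- σ = 0.8: SE = 0.8 × 0.866 × 0.155 = 0.108; 0.357 / 0.108 = 3.32; Φ(1.36) = 91%.
- σ = 1.0: SE = 0.134; 0.357 / 0.134 = 2.65; Φ(0.69) = 76%.
- σ = 1.2: SE = 0.161; 0.357 / 0.161 = 2.21; Φ(0.25) = 60%.

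**Check 2: effect set so that the log-scale analysis has about 80% power.** Check 1 is near its ceiling at σ = 0.5, so it cannot show a loss there. Here the log effect is d = (1.960 + 0.842) × σ × √(1 − ρ²) × √(2/n), with n = 85, ρ from 0.3 to 0.7 and 10,000 trials per setting. For example, at σ = 0.8 and ρ = 0.5, d = 2.802 × 0.693 × 0.153 = 0.298, a ratio of 0.74.

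| σ | Raw-scale power | Points lost against log scale | Share of the outcome's sum of squares from the 5% of participants furthest from the mean |
|---|---|---|---|
| 0.3 | 77% | 2–3 | about 33% |
| 0.5 | 71–73% | 6–8 | 43% |
| 0.8 | 61–65% | 14–19 | 58% |
| 1.0 | 50–58% | 21–29 | 67% |
| 1.2 | 43–51% | 28–36 | 74% |

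Results at 98 per arm are nearly the same.

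**Type I error.** With no true effect, raw-scale ANCOVA rejected in 4.0% to 5.3% of trials across all settings, so the test stays valid.

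**The case against.** **The document does not say raw scale.** A reader might infer that the sponsor has committed to untransformed analysis. That is inferred from silence, and a condensed article may leave transformation to the full protocol or SAP. This stands as a limit on the wording. It does not dispose of the point, because the model, the covariate and the effect measure are stated for every secondary outcome. An ordinary log-scale analysis would be reported as a ratio, so a fuller document that used one would depart from the published effect measure for these markers.

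**Skew is assumed.** A reader might take all three markers to be known to be strongly skewed. The document gives no distribution for any of them. The loss depends on the assumed log-scale SD and need not be the same for Hs-CRP, NSE and HCY. This stands.

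**The simulation favours the log scale by construction.** The data are exactly log-normal with a proportional effect, and no additive effect or other distribution was tried. This stands. The figures show the possible size of the loss under that model and are not a forecast for this trial.

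**Two stronger readings fail.** One is that skew would produce false positives; the type I error results show otherwise. The other is that a single intercurrent infection would dominate the result; no such outlier was simulated, so this is not shown.

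**The baseline rank test proves little.** A reader might infer that the authors foresaw non-normal outcomes. Section 2.13 gives no condition for using that test, and it could serve ordinal baseline items.

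**A mean difference is a legitimate target.** It answers a different question from a ratio of geometric means. This is fair, and it is a reason to keep the mean difference as a supportive description.

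**Conclusion.** The point holds as a minor one. The stated rule covers the three serum concentrations and names no transformation. If a marker is clearly right-skewed, the cost is precision: for an assumed 30% reduction with 83 per arm and ρ = 0.5, about 14 points of power at σ = 0.8 (77% against 91%) and about 24 points at σ = 1.0 (51% against 75%). For that effect the difference is negligible at σ = 0.5 or below. For a smaller effect, set for about 80% power on the log scale, it is 6–8 points at σ = 0.5 and 2–3 at σ = 0.3.

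These sizes rest on assumed log-normal data, a proportional effect and an assumed σ. Validity is not at issue. The markers are exploratory secondary outcomes with no power claim, and the primary analysis is untouched.

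**What to change.** Before unblinding, prespecify for Hs-CRP, and for NSE and HCY on the same basis:
- ANCOVA on log-transformed follow-up values, with log baseline as covariate and treatment as a factor;
- centre as a further factor. Section 2.6 stratifies randomisation by centre, but the model in section 2.13 omits it. This is a separate small improvement, unrelated to skew;
- the effect reported as a ratio of geometric means with 95% CI.

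The raw mean difference may stay as a supportive description. The multiple imputation in section 2.13 should use the same log scale for these markers, so that imputed concentrations cannot be negative.

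The cost is wording only: no change to sample size, visits or data collection. The downside is that readers see a ratio instead of a difference in concentration units. If the full protocol or SAP already fixes a log-scale analysis for these markers, it is enough to align the effect measure in section 2.13 with it.

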## Discussion

3

Vascular dementia is an enormous, worldwide public health problem. Traditional Chinese medicine is an important complementary and alternative medicine, which has been used for treatment of dementia-like symptoms for centuries. SMYZD, a Chinese herbal formula, was used as an adjuvant treatment of VaD in clinical practice in China. Preclinical studies support that SMYZD could intervene in complicated molecular pathways underlying the pathogenesis of VaD. The main aim of this study is to investigate the effect of SMYZD as an adjuvant role in the treatment of AD.

In the present study, besides using the ADAS-cog, MMSE, ADL and TCM symptom scales to assess the clinical curative effect on cognitive function, NIHSS will be introduced to evaluate neurological status. In addition, we monitor the serum concentration of Hs-CRP, NSE and HCY to explore the possible mechanism of SMYZD combined with GBEs on treating VaD.

This study also has some limitations. For example, this study is limited to 1 region (Beijing). It is unclear whether our findings will be representative of other regions of China.

In conclusion, findings of this study are expected to provide evidence for efficacy and safety of SMYZD as an adjuvant treatment of VaD.
